#### Sample Size Calculations

Given the planned study design with two treatment conditions (real and sham tDCS), two time points (before and after the intervention) and three diagnostic groups (anxiety, depressive and conduct disorder), a repeated-measures analysis of variance (rmANOVA) with the following parameters was set up: α = 0.0167 (0.05 corrected for three groups), power 1 – β = 0.80, a moderate effect size of f = 0.25 (73). The FEEL-KJ [German version of the Questionnaire for the assessment of emotion regulation in children and adolescents; (74)] as it is used for assessment of the primary endpoint was reported to have a test-retest reliability of r = 0.62, a Chronbach alpha of α = 0.93 for the adaptive strategy subscale and a Chronbach alpha of α = 0.82 for the maladaptive strategies, whereas for the 15 different emotion specific subscales Chronbach alphas between α = 0.69 – α = 0.91 were reported (74). Non-sphericity is of no relevance for only two repeated measures. This, results in a required sample size of 36 per group and 108 subjects overall.

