#### Electrode Placement and Current Strength

Due to the inter-individual variability in the response to tDCS in adult studies (79, 80) as well as the specific features of the stimulation-generated electric fields' behavior in the youth population (81), a suggestion in the pediatric tDCS literature for simulation-based stimulation protocols has been brought up (53, 58). MRI-based finite-element models of the human head can assist parameter choice and dose individualization through the estimation of the spatial distribution and the magnitude of the electric fields (82). In children and adolescents, due to the fast changes in the anatomical characteristics (gray matter alterations, bone thickness, cortical-spinal fluid quantity), field magnitudes are usually 1.5–2 times higher than in the adults (83, 84).

Therefore, in this clinical trial, in an attempt to increase spatial precision in targeting the non-superficial cortical area of the vmPFC, an optimized high definition, multi-channel montage based on computational simulations, was chosen. For this reason, the optimization was conducted with the Stimweaver algorithm (Stimweaver montage optimization service from Neuroelectrics NE, Barcelona) to determine the positions of the computed 8 electrodes and required currents for the vmPFC (Figure 2). Based on two head models (male/female) generated from structural T1 images from adolescents within the same age range from a previous clinical trial ran by our research group, an optimized montage for female and male participants was calculated. For female participants anodal stimulation will include electrode positions FP1, FP2, FPz, and P08, while cathodal electrodes will be placed at electrode positions FC1, FC2, and Fz. For male participants anodal stimulation will include electrode positions FP1, FP2, and O1, while cathodal electrodes will be placed at electrode positions FC1, FC2, Fz, and F4. The maximal injected current into the brain at any given time will be below 2.00 mA and maximum current at any electrode is 1.00 mA. The electrodes used in this study are 1 cm radius Ag/AgCl cylindrical electrodes with conductive gel underneath (NG PiStim electrodes).

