Single-subject analysis of the fMRI data will be conducted using the general linear model (GLM) as implemented in SPM12. The conditions will be modeled as previously described for the eSTROOP (120), e-nBACK (124) and the ERT [similar to (123)]. Image-derived movement estimates and surrogates of physiological artifacts (heartbeat, breathing) will be used as covariates and regressed out. The same corrections will be applied to the RS data, which will be used for estimating functional connectivity using in-house software. Group analyses of the whole-brain fMRI data will be again conducted using the GLM in SPM12. The Sandwich Estimator (SwE) will additionally be utilized for missing data. Diagnostic group and measurement (pre-/post-intervention) will be used as model factors. Subject age and sex will further be corrected for on group-level. Besides factorial group analysis, exploratory correlations will be calculated with indicators of disorder-specific impairments and emotion regulation capabilities. For multiplicity correction, SPM12 uses random field theory based on the smoothness of the data and SwE a bootstrapping approach.

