## Discussion

Here, a transdiagnostic, randomized, triple-blinded and sham-controlled neurotherapeutical brain stimulation trial is presented. From a translational perspective, this study promises high rewards to both: basic research in neuroscience as well as the fields of mental health. Regarding the former, by targeting one of its assumed neural substrates, we aim to add causal evidence to the involvement of the vmPFC in pathologies of emotion regulation. Further, we would establish a proof that anodal tDCS in combination with an optimized, multi-electrode montage can efficiently affect the targeted emotion regulation deficits via the modulation of one of its neural underpinning, namely the vmPFC. In contrast to previous tDCS studies, the simulation and modeling for the multi-electrode montages were based on MRI measures of both sexes, as well as in the optimal age range, adding specificity to the stimulation protocol. Electrical stimulation protocols aiming to target neural networks for e.g., changing the inhibitory/ excitatory balance in different brain regions [e.g., (125)] would be interesting for future endeavors, if evidence is repeatedly shown.

As the intervention has promising applications in psychiatry, it is important to point out, that the current project provides the first empirical, transdiagnostic tDCS therapy attempt in adolescents with depressive, anxiety and conduct disorders. With this approach, we aim to overcome disadvantages of standard therapies like side effects of or insufficient commitment to medication, long durations and related costs. Therefore, we developed a specific therapeutic brain stimulation procedure to achieve the greatest possible commitment on the patients' side, as well as the greatest possible neuromodulative effect. The training paradigm is built for the purpose to activate cognitive and emotional brain networks at the same time: brain regions involved in cognitive functioning (e.g., prefrontal areas), through the required actions during the tasks and at the same time brain regions involved in emotional functioning (limbic areas, e.g., amygdala), through the presentation of emotional stimuli. With this procedure, we expect to activate those brain areas through the training paradigm, which are simultaneously stimulated with tDCS.

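### The stated fMRI group analysis is a whole-brain search with no vmPFC-specific test, so it is poorly matched to the aim of showing action via the vmPFC and may be badly underpowered for it

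*Protocol article*

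**What the plan says.** The Introduction selects the vmPFC as the one region that meets both of the authors' requirements for a stimulation target. Its section on the neural basis of emotion regulation describes the route as vmPFC inhibition of the amygdala. Under Electrode Placement and Current Strength, separate male and female montages are optimised for that region from head models; the motivation given is that "MRI-based finite-element models of the human head can assist parameter choice and dose individualization". The Discussion looks forward to causal evidence about the vmPFC and to a proof that stimulation affects emotion regulation "via the modulation of one of its neural underpinning, namely the vmPFC".

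The fMRI paragraph of Statistical Analysis states the group test: "Group analyses of the whole-brain fMRI data will be again conducted using the GLM in SPM12". On error control it says "For multiplicity correction, SPM12 uses random field theory based on the smoothness of the data", with a bootstrap for the Sandwich Estimator. It does not say whether inference is at voxel or cluster level. Resting-state functional connectivity and exploratory correlations are also planned, without a named seed or connection. Outcomes places brain activation and connectivity among the measures to be explored.

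**The concern.** With a single target fixed in advance, the direct question for the scanner is whether that region changed more under real than under sham stimulation. A whole-brain search asks whether anything changed anywhere, and pays for it with a much stricter threshold. If the corrected map is empty, nobody can tell an unmodulated vmPFC from a threshold that was too strict. If a cluster appears elsewhere, it does not by itself support the stated mechanism. Better scores on a questionnaire cannot show that the vmPFC was modulated either; the MRI is the trial's only direct measure of it. What is at stake is the mechanistic claim in the Discussion, not the clinical result.

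**Working it through.** **The plan's own figure.** Sample Size Calculations gives "α = 0.0167 (0.05 corrected for three groups", "power 1 – β = 0.80", "a moderate effect size of f = 0.25" and a "test-retest reliability of r = 0.62". For the arm-by-time interaction with m = 2 time points, λ = f²·N·m/(1 − ρ). With N = 36, λ = 0.0625 × 36 × 2 / 0.38 = 11.84 on F(1, 34), and power is 0.816. N = 35 gives 0.803 and N = 34 gives 0.788, so 36 is the smallest size with two equal arms. Three diagnostic groups make 108, and the stated figure reproduces. It concerns the FEEL-KJ only; no fMRI effect size or power is given.

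**Inputs for the imaging check.** From Stratification and Randomization: 54 per arm. Assumed: a standardised difference d in the pre-to-post change of 0.5 or 0.8, and voxel thresholds of t = 4.5-5.0. Power comes from the noncentral t with df = 2n − 2 and noncentrality δ = d·√(n/2).

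- d = 0.5, n = 54: δ = 0.5 × √27 = 2.60.
- d = 0.8, n = 54: δ = 0.8 × √27 = 4.16.
- d = 0.5, n = 45 (assumed scan loss): δ = 0.5 × √22.5 = 2.37.

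| Case | Region mean, 0.05 | Region mean, 0.025 | Given voxel, t = 4.5 | Given voxel, t = 5.0 |
|---|---|---|---|---|
| d = 0.5, n = 54 | 73% | 63% | 3.5% | 1.2% |
| d = 0.8, n = 54 | 98% | 97% | 38% | 22% |
| d = 0.5, n = 45 | 65% | 54% | 2.2% | 0.7% |

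For d = 0.5 and n = 54, the region mean has 57% at 0.0167 and 53% at 0.0125 (alpha shared over four functional scans).

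**Is t = 4.5-5.0 a fair threshold?** For an assumed brain volume of 1.2-1.5 litres and smoothness of 6-12 mm, random field theory at familywise 0.05 gives T of about 4.9-5.5 one-sided, or 5.1-5.7 two-sided. Power at a given voxel for d = 0.5 is then 0.4-1.6% or 0.2-1.0%, so the range in the table is lenient. A voxelwise small-volume correction over 10-40 cm³ reaches only about 4-12%. The gain therefore comes from testing one regional summary, not just from searching a smaller volume.

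**Detection anywhere in the region.** This was simulated with 8 mm smoothness and a signal of 10-15 mm radius, under assumed amounts of spatially shared variation.

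- Signal set so that the region mean has d = 0.5: a peak above T = 5 in 1-10% of runs; a cluster (forming threshold p < 0.001, extent above 800-1,600 mm³) in 0-40%.
- Signal set so that every voxel has d = 0.5: a peak above T = 5 in 9-74%; a cluster in 19-93%. In these runs the region mean itself has d between 0.55 and 1.81, so they are not like for like with the 73%.

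**The protocol's own meaning of moderate.** Carrying f = 0.25 over to all 108, λ = 0.0625 × 108 × 2 / (1 − ρ). With ρ = 0.5, λ = 27.0 and δ = 5.20; with ρ = 0.62, λ = 35.5 and δ = 5.96. One-sided whole-brain voxel power is then 40-63% or 68-85%. Dividing δ by √27 gives d = 1.00 and 1.15, about twice the value used above. The 0.62 is a questionnaire reliability, so its use for fMRI is also an assumption.

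**The case against.** The article is condensed. It gives the fMRI analysis one paragraph, calls no fMRI test primary and does not rule out a regional test; a mask and named contrasts may sit in the full protocol or analysis plan. Brain measures are listed as exploratory, and a whole-brain analysis suits the general purpose of describing changes in brain response. The Discussion sentence about proof is conditional, and the same section concedes that results cannot be reduced to stimulation alone. Setting one uncorrected region test against one corrected voxel also flatters the region test.

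Much of this stands. It would be wrong to say that the plan picked the wrong primary fMRI test, because it designates none. The fair power figure for a two-test scheme is 63%, not 73%. A reader might also infer that the trial cannot answer its question about the vmPFC. That goes too far: connectivity analyses are planned, an effect in a connected area such as the amygdala could bear on the mechanism, and a regional contrast would not by itself show that benefit runs through the vmPFC.

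What remains is that the article does describe the group analysis, including search volume and error control, and what it describes is not aimed at the region on which the rationale and the claim rest. Calling the measures exploratory does not fit with a hope of proof.

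**Conclusion.** The mismatch between the stated fMRI test and the vmPFC-specific aim holds. Its size depends on assumptions. At d = 0.5 on the change with 54 per arm, one region mean has 63-73% power, against about 1-4% at a given voxel at t = 4.5-5.0.

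A reader might infer from this that target engagement has almost no chance of being detected at a moderate effect. The documents do not support that. It requires voxel-level inference, d = 0.5 on the change and detection counted at one given voxel, and the article states none of these. Cluster-level inference could lie anywhere from near zero to above 73%, and the protocol's own f = 0.25, if carried over to fMRI, gives 40-85% at a voxel. The supportable wording is that the stated test may be badly underpowered for this aim. The point is a cheap improvement that should be made. It leaves the FEEL-KJ analysis untouched.

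**What to change.** Before unblinding, add to the fMRI analysis:

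- One pre-specified vmPFC region, for example from the field models already made for the two montages, or an anatomical mask if these do not give one usable region.
- The real-versus-sham by time contrast of the region mean, in one named task contrast, as the lead fMRI test of target engagement. This needs stimulation condition in the group model; the listed factors are diagnostic group and measurement time only, which is a separate matter to correct.
- vmPFC-amygdala resting-state connectivity as a second test, with alpha shared between the two (for example 0.025 each).
- The whole-brain maps kept, labelled exploratory.

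If the full plan already holds such a test, one sentence in the article would settle the point. If no regional test is adopted, soften the Discussion's claim of proof through vmPFC modulation.

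The cost is analysis wording and a mask; no new data or participants are needed. The downside is commitment in advance to one region and one contrast: a mask that includes much unaffected tissue would dilute the effect, and a poorly chosen contrast could miss it.

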#### Secondary Hypotheses

We expect significant improvements in disorder-specific clinical symptomatology, quality of life, as well as in emotion recognition and regulation, attentional bias and working memory (in the related psychological, behavioral and physiological indices) in the experimental group, compared to the control group after the interventions.

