### Outcomes

The primary outcome of this study is the change in emotion regulation ability, measured by the raw score of the FEEL-KJ (74). Here, we expect an increase in emotion regulation after the intervention of the experimental group in total (as well as for each clinical experimental subgroup) compared to the control group in total (as well as for each clinical control subgroup).

As exploratory outcomes, we will investigate if the application of tDCS improves the disorder-related clinical symptomatology, quality of life or emotion regulation, whereas changes in raw scores of the related self- and parental reports (as summarized in Psychological Self- and Parental Ratings) are defined as secondary endpoints.

Further we will explore if indices of emotion recognition [measured via Frankfurter Test and Training for Recognizing Facial Affect (FEFA II) and the Emotion Recognition Task (ERT)], and (implicit) emotion regulation (measured via eSTROOP) improve from before to after tDCS stimulation. In addition, measures of attentional bias [*via* Attentional Bias Task (ABT)] and working memory (*via* e n-BACK) will give insight regarding potential improvements in the related indices from before to after tDCS stimulation. Indices of each task (such as the number of correct behavioral assignments, commission, omission, reaction times, eye gaze fixation duration, pupil dilation, brain activation, brain connectivity) are summarized in Eye Tracking and Behavioral Measures and fMRI Procedure and Measures.

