### Statistical Analysis

Regarding the primary endpoint, repeated-measures analysis of variance (rmANOVA) with Time (pre/post) and Treatment Condition (real stimulation/sham stimulation), as well as considering the three clinical subgroups will be conducted to investigate the interaction between times and groups on the dependent variable [FEEL-KJ raw scores (74)]. The sex and age of the participants will be used as blocking factor accounting for treatment variability between males and females and the three age groups, respectively. In the case of distributions not suitable for conventional testing and missing values, a generalized linear mixed model on the relationship between the stimulation condition and behavioral variables can be applied. Stimulation condition and time will be taken as the fixed-effect factors and the participant's ID as the random-effect factor. Parameters of the model will be fitted with the maximum-pseudolikelihood method, the appropriate distribution and link function according to the characteristics of the response data. A marginal ANOVA will follow to evaluate the fix-effect factors significance. The secondary endpoints, i.e., the indicators for aggression, depression, anxiety and quality of life, as well as cognitive and emotional functioning will be compared using the same approach. In order to identify the direction of effects, *post-hoc* tests will be employed.

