Here, specific training effects have to be considered regarding potential biases in outcome measures. Both treatment groups undergo the described emotion regulation training, regardless of receiving real or sham stimulation. Therefore, we will not be able to reduce our results to the pure effect of the activation via tDCS since an induced modulatory training effect is actually desired. Moreover, the emotion regulation training itself might lead to improvements in both groups. If group differences in the improvements of the clinical outcome measures become insignificant, future research will be needed to differentiate between the training and stimulation influences. Only after this analysis, it is possible to clarify if only the developed emotion-cognition training procedure alone is sufficient for an effective training or if the brain stimulation further increases the therapeutic effect. In this case, also the influence of the engagement in the study *per se* would need to be investigated via a suitable control condition.

As the here presented clinical therapy trial not only includes three groups of patients and a novel brain stimulation procedure, but also pre- and post-measures on multiple levels (subjective psychological measures via self- and parent-rated questionnaires, behavioral and eye tracking tests, neuronal measures via MRI), inclusions of further diverging control groups would have gone beyond the scope of this single study.

Considering the developmental psychophysiological perspective, this project does not only highlight the treatment advantages of the excitability of the adolescent brain, it also takes the chance to possibly intervene early enough to hinder a further worsening of the clinical symptoms of depressive, anxiety or conduct disorders and the pathological manifestations in adulthood.

Utilizing a transdiagnostic approach for the treatment of emotion dysregulation as a common factor in anxiety, depressive and conduct disorders, this study is oriented toward a dimensional perspective on mental health as it was formalized in the Research Domain Criteria framework. If successful, this project will provide a non-invasive therapeutic option for the most prevalent psychiatric disorders in adolescents, with the possibility to transfer the protocol to related conditions in future studies.

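### The fMRI group model omits real versus sham, so as written it cannot test the imaging part of the secondary hypothesis

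*Protocol article*

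**What the plan says.** The Statistical Analysis section describes two different models.

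- **Primary endpoint.** A repeated-measures ANOVA with "Time (pre/post) and Treatment Condition (real stimulation/sham stimulation), as well as considering the three clinical subgroups". The section then extends the same approach to the secondary endpoints, which it lists as indicators of aggression, depression, anxiety, quality of life, and cognitive and emotional functioning.
- **Whole-brain fMRI.** A separate paragraph gives a group-level GLM in SPM12, with the Sandwich Estimator (SwE) added for missing data. Its factors are stated: "Diagnostic group and measurement (pre-/post-intervention) will be used as model factors". So are its covariates: "Subject age and sex will further be corrected for on group-level". The only other group-level analysis is that "exploratory correlations will be calculated with indicators of disorder-specific impairments and emotion regulation capabilities". Real versus sham appears nowhere in this paragraph.

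Secondary Hypotheses predicts improvement in "attentional bias and working memory (in the related psychological, behavioral and physiological indices) in the experimental group, compared to the control group". Outcomes names "eye gaze fixation duration, pupil dilation, brain activation, brain connectivity" among the indices of the tasks.

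**The concern.** The hypothesis compares the randomised arms, and the imaging model does not contain the arms. Its measurement effect is the pre/post change averaged over everyone scanned, whichever stimulation they received.

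That matters more here than in many trials, because change without active stimulation is expected. The Discussion says that both arms receive the training and that "the emotion regulation training itself might lead to improvements in both groups". According to Stimulation Protocol and Intervention Procedure, the emotion recognition task and the emotional n-back are performed during the sessions in both arms. fMRI Procedure and Measures uses versions of these same two tasks as scanner paradigms. Practice, repeat scanning and stimulation would therefore all enter the same coefficient. Outcomes also words the task indices as change from before to after stimulation, which makes it easy to read a pooled change as an effect of tDCS.

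**Working it through.** The plan gives no effect size or sample-size figure for imaging, so there is no stated number to reproduce. The 108 was calculated for the FEEL-KJ and does not bear on this point. The check is whether the arm difference can be estimated from the model as written.

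**Inputs**
- 108 participants, 36 per diagnosis, 18 real and 18 sham in each (Stratification and Randomization).
- Two MRI sessions per participant, before and after the intervention; the follow-up visits have no MRI (Procedure and Intervention).
- Model as written: diagnosis and measurement, adjusted for age and sex (Statistical Analysis). The check gives each diagnosis its own pre/post change, the most flexible form that these two factors allow. Age and sex are constant within a participant as entered and balanced across arms by design, so they do not supply the missing contrast.

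**What the measurement effect estimates**

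Let *c* be the mean pre/post change under sham (training, retest, repeat scanning) and *d* the real-minus-sham difference in change. The real arm then changes by *c* + *d*. Within each diagnosis the fitted change is

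(18 × *c* + 18 × (*c* + *d*)) / 36 = *c* + *d*/2.

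| Sham change *c* | Stimulation effect *d* | Fitted change, every diagnosis | *d* recovered once condition × measurement is added |
|---|---|---|---|
| 0.5 | 0 | 0.5 + 0 = 0.5 | 0 |
| 0.25 | 0.5 | 0.25 + 0.25 = 0.5 | 0.5 |
| 0 | 1.0 | 0 + 0.5 = 0.5 | 1.0 |

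The values are illustrative and in arbitrary units. The model as written returns the same answer for no stimulation effect and for a large one. It can also hide a real effect: with *c* = −0.25 and *d* = 0.5, the fitted change is −0.25 + 0.25 = 0.

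**Whether another term in the model rescues it**

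- The diagnosis × measurement interaction compares change between diagnoses. Each diagnosis holds the same 1:1 mix of arms, so this contrast does not carry the arm difference either.
- With participant effects included, the design has rank 108 + 3 = 111. Adding a condition × measurement column raises it to 112. The added column is therefore not a combination of the existing ones, and the arm difference is not estimable until it is included.
- Without participant effects, diagnosis and diagnosis × measurement give rank 6. Adding condition and condition × measurement gives rank 8, and the conclusion is the same.

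**Unequal numbers of scans**

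If a share *p* of the complete scan pairs comes from the real arm, the fitted change is *c* + *p* × *d*. Missing scans move the weight away from one half, but they do not separate *c* from *d*.

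**The case against.** The best defence is that the paragraph does not call its factor list exhaustive, and that this is a condensed article. The preceding paragraph sets time by treatment condition as the trial's framework and applies the same approach to cognitive and emotional functioning, which are the domains the scanner tasks probe. On that reading the fMRI paragraph only adds technical detail, or diagnostic group is a slip for treatment group. The sham-controlled intent is plain throughout and arm is known for every participant, so the right test stays available.

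This does not remove the point. The sentence about the same approach does not name imaging, and it is followed by a different, specific list for imaging that goes down to age and sex. A reader following the text would fit the model without arm. If the wording is a slip, it needs the same correction.

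Four parts of the defence do stand:
- Outcomes reserves the term secondary endpoints for questionnaire raw scores and introduces the task indices as exploratory, so the imaging results sit at a lower tier.
- Physiological indices also include gaze and pupil measures, which the first model can cover.
- Nowhere do the authors say that they will report a pooled change as a tDCS effect, and the Discussion shows that they know about training effects. Misattribution is a risk of the stated model and not a declared plan.
- With no fMRI effect size in the document, the practical size of the bias cannot be given.

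**Conclusion.** The concern holds: the fMRI group model is wrong as written for the hypothesis it serves. Run literally, it estimates the sham-arm change plus half the stimulation effect and has no term for the randomised comparison. The factor of one half assumes complete scans with equal arms; the absence of the contrast does not depend on that. The defect is confined to the whole-brain fMRI group analysis, including connectivity if it is analysed with the same model. The primary FEEL-KJ analysis, the questionnaire endpoints, the behavioural and eye-tracking indices and the sample size are not affected.

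**What to change.** Rewrite the sentence in Statistical Analysis so that the imaging group model has stimulation condition (real/sham) and measurement (pre/post) as factors, with the condition × measurement interaction as the tested contrast. Apply it to the three task paradigms and to the resting-state connectivity data, and use the same contrast in the SwE model. Keep age, sex and diagnosis; whether diagnosis enters as a factor (with a three-way term, if differences between disorders are of interest) or as a covariate is the team's choice. State that the pooled pre/post effect is descriptive and will not be read as an effect of tDCS.

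With two scans per participant, the contrast amounts to comparing post-minus-pre images between arms. Coded arm labels are enough, so analyst blinding can be kept. The cost is about one sentence, with no extra participants or scans, and it should be made before the allocation is unblinded.
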